### Recruitment {15}

The dissemination and recruitment of participants for the research will be done through advertisements (internet, radio, and posters) in the city of São Carlos. The dissemination of the research will also be carried out in all health units in the city and in the university’s internal media, with the collaboration of other research departments for the recruitment of individuals.

### Assignment of interventions: allocation

#### Sequence generation {16a}

The individuals included in the study will be randomized via the website (randomization.com). In this selection process, the site will generate a random sequence, and each individual will be randomized into a single group using the permuted block method, 14 blocks with 6 each, totaling 84 in total. Then, they will have the same probability of being drawn and allocated into one of the 3 study groups: traditional acupuncture [TA] (individuals who will receive acupuncture intervention with needles), laser acupuncture [AL] (individuals who will receive laser acupuncture intervention), and sham [S] (subjects who will receive placebo intervention). The researcher, responsible for the randomization, will have no other role in this study.

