### Who will take informed consent? {26a}

Data collection will only start after the participants have signed an informed consent form, which will be explained by the evaluator.

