#### Strategies to improve adherence to interventions {11c}

To minimize data loss, all the participants in the trial will receive a card with the date and time of session. The therapist responsible for the session will send a WhatsApp message from a cellphone account used only for this research, confirming the session, 1 day in advance. For the evaluations and reevaluations, the blinded evaluator will contact the participants by WhatsApp, confirming the initial and final evaluations, as well as the follow-up 1 month after the end of the intervention, which will be performed by telephone. In cases of abandonment or impossibility of continuing the study, the data will be analyzed according to an intention-to-treat protocol.

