### Sample size {14}

The calculation of the sample size considered a difference of 1.5 points between the groups, which would be a clinically relevant value for the outcome of neck pain intensity, as measured using the Numeric Rating Scale (NRS) [64, 66], with an estimated standard deviation of 1.6 points, based on a scientific clinical study [43]. There are a statistical power of 80% and a possible sample loss of 20%, considering individuals who for any reason want to interrupt the intervention. Thus, 84 individuals will be needed in total, 28 in each group (TA, LA, and Sham). The processing of the sample calculation was performed using the Minitab software, v.17, State College, PA.

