#### Concealment mechanism {16b}

After the website (http://randomization.com) generates a numerical sequence for an allocation, the concealment of selected individuals will be achieved through opaque sealed envelopes, which will be stored in a safe cabinet that only the allocation investigator will have access to. The envelopes will be opened immediately before the intervention by the researcher responsible for applying the treatments.

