#### Implementation {16c}

This study will have five researchers who will be independently specialized, and each one of them will have a function. The researcher, mastering (R1), will be responsible for recruiting and registering the participants. The researcher (R2) will be responsible for randomization and for generating a random allocation sequence. The researcher (R3) will only be responsible for applying the interventions (TA, LA, and SHAM). The researcher (R4) will carry out all research evaluations (NRS, PPT, TS, CPM, GPE, use of analgesic medications after treatments). The last researcher (R5) will analyze and register the data.

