### Assignment of interventions: blinding

#### Who will be blinded {17a}

The evaluator will be blinded to the randomization and intervention processes, be responsible only for recruitment and evaluations, and receive no information regarding the allocation of the individuals to the groups. The participants and the researcher responsible for the treatment will not be blinded, due to the nature of the interventions.

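### A constant block size of 6 makes about one allocation in five foreseeable to the single unblinded therapist, and the article names two different recruiters

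*Protocol article*

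**What the plan says.** Sequence generation {16a} of the Protocol article describes a list made by "using the permuted block method, 14 blocks with 6 each, totaling 84 in total", and adds that "they will have the same probability of being drawn and allocated into one of the 3 study groups". Sample size {14} gives 84 participants, 28 per arm. Study setting {9} names one site, and no stratification factor is stated, so there is one running sequence.

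Under Concealment mechanism {16b}, "The envelopes will be opened immediately before the intervention by the researcher responsible for applying the treatments". Intervention description {11a} has the same acupuncturist (R3) give all treatments, and Who will be blinded {17a} says this person is not blinded. Strategies to improve adherence to interventions {11c} says: "The therapist responsible for the session will send a WhatsApp message", sent one day ahead to confirm the session.

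On roles, Implementation {16c} says that R1 "will be responsible for recruiting and registering the participants", confines R3 to applying the interventions and gives the evaluations to R4. Who will be blinded {17a} instead has the evaluator "be responsible only for recruitment and evaluations", and says that the evaluator is told nothing about allocation. Who will take informed consent? {26a} adds that the consent form is one "which will be explained by the evaluator".

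**The concern.** Sealed envelopes conceal the next assignment only if it cannot be inferred from earlier ones. With a constant, published block size and one sequence, whoever has seen all earlier assignments knows the end of every block. R3 has seen them all, and is in contact with the next participant before that participant's envelope is opened.

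If foreknowledge influenced who came forward at a given point, even unintentionally, the arms could differ at baseline. The primary outcome is self-reported pain on the NRS and each arm has only 28 people, so a small shift in case mix could matter. The article's separation of roles is the main safeguard, and its own sections disagree on who recruits.

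**Working it through.** **Inputs.** From Sequence generation {16a}: 14 blocks of 6, three arms, equal probability. Assumption: the observer knows the block size and every earlier assignment, and can tell all three arms apart. Only R3 fits this description.

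**The plan's own figure.** 14 × 6 = 84; 84 / 3 = 28 per arm; 6 / 3 = 2 per arm in each block. The list length reproduces.

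**Certain assignments, fixed block of 6.** There are 6!/(2!·2!·2!) = 90 possible orders. An assignment is certain when all remaining places in the block belong to one arm.
- Places 1 to 4: never certain, because at least three places remain and no arm has more than two.
- Place 5: certain if the last two places share an arm, 3 of the 15 possible pairs = 0.20.
- Place 6: always certain, 1.00.
- Sum: 0.20 + 1.00 = 1.2 per block; 1.2 / 6 = 20%; 14 × 1.2 = 16.8 of 84.

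**Best-guess rate, same observer.** This is the expected share of the remaining places held by the commonest remaining arm.
- Place 1: 2/6 = 0.333
- Place 2: 2/5 = 0.400
- Place 3: 2/4 = 0.500
- Place 4: 0.4 × 1/3 + 0.6 × 2/3 = 0.533 (the three remaining places are one of each arm with probability 8/20)
- Place 5: 0.2 × 1 + 0.8 × 1/2 = 0.600
- Place 6: 1.000
- Sum 3.367; 3.367 / 6 = 56.1%, against 33.3% by chance.

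At least one arm can be ruled out with probability 0, 0, 0.2, 0.6, 1 and 1 at the six places: 2.8 / 6 = 46.7% of assignments.

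**An observer who learns only needle versus laser-type treatment.** Each block then holds two needle and four laser-type places. Certainty by place, from the third: 1/15, 4/20, 7/15, 1. Sum 1.733; 1.733 / 6 = 28.9%, about 24 of 84. This is certainty about treatment type, not arm, and it requires that treatment type leaked every time.

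**Alternatives.** A larger constant size, if known, helps only in part: simulation gives 14.3% certain for blocks of 9 and 11.1% for blocks of 12. Randomly ordered blocks of 6, 9 and 12 do more. Simulating an observer who updates on past assignments gives about 2.5% certain when sizes and mix are unknown and about 4% when the mix is known. The best-guess rate is about 53%.

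**Roles side by side.**
- Recruitment: R1 in Implementation {16c}, the evaluator in Who will be blinded {17a}. Since Implementation {16c} makes R4 the evaluator, the two cannot both hold.
- R3: interventions only in Implementation {16c}, but also the appointment message in Strategies to improve adherence to interventions {11c}. These fit badly.

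**The case against.** The strongest reply is that no one person is shown to have both the allocation history and an enrolment role. R3 has the history, but is not named as recruiter, screener or consent-taker. The message is a reminder of a date and time already on the participant's card, and nothing lets R3 schedule, refuse or reorder participants. The envelopes stay in a cabinet that only the allocation investigator can open. All of this stands, and it limits the point to a risk.

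A reader might infer that one allocation in five is certain to the staff who recruit. The documents do not support that. The evaluator, whom one section makes recruiter, is by the same section told nothing about allocation. The evaluator does see participants straight after treatment, and Limitations accepts that needle and laser cannot be blinded from each other for participants, so a leak is possible, but it is not stated. Even then, real and sham laser use the same device and sounds, so only treatment type could be predicted.

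A reader might also take the consent section to contradict Implementation {16c}. It does not: Implementation {16c} is silent on consent, and a blinded evaluator explaining the form is not an error.

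Finally, mixed blocks barely change the best-guess rate. That is true. The gain is in assignments known with certainty.

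**Conclusion.** The point holds in a limited form. To R3, 20% of assignments (about 17 of 84) are certain in advance and 56% can be guessed correctly. This assumes that R3 knows the block size, which the article prints, or deduces it from the sequence. R3's contact with participants before allocation gives some scope for informal influence, but no documented power over enrolment. This is a predictability risk, and selection bias is not shown.

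The conflict over who recruits is a plain contradiction and needs correcting whatever block design is used. R3's reminder task should likewise be squared with the limit on R3's role. Together these are worth fixing because the remedy is cheap; they do not invalidate the design.

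**What to change.** 1. R2 generates the list with randomly ordered blocks of mixed sizes. For a full list, two blocks of 6, four of 9 and three of 12 give 12 + 36 + 36 = 84, with 4 + 12 + 12 = 28 per arm. Trial status dates the start of recruitment to March 2021; if enrolment has begun, apply mixed blocks to the remaining participants only.
2. Withhold block sizes and mix from R1, R3 and R4, and keep them out of documents these staff use.
3. Send appointment messages from R1 instead of R3.
4. Name one recruiter consistently in Implementation {16c} and Who will be blinded {17a}.

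The cost is a new list and wording changes, with no extra staff or participants. The downside is possible slight imbalance if recruitment stops inside a larger block: two arms can then differ by at most 4 in a block of 12, against 2 in a block of 6.

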#### Concealment mechanism {16b}

After the website (http://randomization.com) generates a numerical sequence for an allocation, the concealment of selected individuals will be achieved through opaque sealed envelopes, which will be stored in a safe cabinet that only the allocation investigator will have access to. The envelopes will be opened immediately before the intervention by the researcher responsible for applying the treatments.

#### Implementation {16c}

This study will have five researchers who will be independently specialized, and each one of them will have a function. The researcher, mastering (R1), will be responsible for recruiting and registering the participants. The researcher (R2) will be responsible for randomization and for generating a random allocation sequence. The researcher (R3) will only be responsible for applying the interventions (TA, LA, and SHAM). The researcher (R4) will carry out all research evaluations (NRS, PPT, TS, CPM, GPE, use of analgesic medications after treatments). The last researcher (R5) will analyze and register the data.

### Assignment of interventions: blinding

#### Who will be blinded {17a}

The evaluator will be blinded to the randomization and intervention processes, be responsible only for recruitment and evaluations, and receive no information regarding the allocation of the individuals to the groups. The participants and the researcher responsible for the treatment will not be blinded, due to the nature of the interventions.

#### Procedure for unblinding if needed {17b}

The evaluator will not be allowed to unblock the blinding. However, the acupuncturist researcher responsible for applying the treatments will not be blinded.

### Data collection and management

#### Plans for assessment and collection of outcomes {18a}

The interventions will follow an application protocol. The evaluator will be trained in the application of the questionnaires and tests, while intra-examiner reliability will be estimated by calculation of ICC.

#### Plans to promote participant retention and complete follow-up {18b}

The participants will be provided with guidance when they sign the informed consent form and commit to attending on the scheduled treatment dates. They will receive a card with the dates of the treatment sessions, a contact telephone number, and a WhatsApp contact number used only for this research. This will ensure that they receive the necessary attention and will assist in fully accompanying them during the research. If individuals abandon the trial, the reasons will be recorded, the most recent data will be computed, and analysis will be performed using the intention-to-treat principle.

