#### The primary objective

The primary objective is to assess the pain intensity at rest and during cervical active movements (flexion, extension, left and right lateral bending, and left and right rotation) using the Numerical Rating Scale (NRS), immediately after the end of the therapies and with follow-up after 1 month.

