### Exclusion criteria

Individuals will be excluded if they present fracture or history of vertebral injury, spondylolisthesis, spinal canal stenosis, ankylosing spondylitis, signs of radiculopathy, cancer, acute infections, hemorrhagic diseases, rheumatologic diseases, systemic inflammatory diseases, diagnostic changes in skin sensitivity, hearing deficits (uncorrected), difficulty in answering questionnaires, in conditions of pregnancy, puerperium and breastfeeding; individuals who have started or underwent any type of intervention or treatment in the last 3 months; individuals who will be orientated not to ingest any sedative, anti-inflammatory and analgesic medications (narcotics and non-narcotics), and any type of alcoholic substance in the last 48 h before the evaluation; individuals who do not comply with the conditions and treatments, or who refuse to participate in the research, will be excluded; individuals who could not remain in the ventral decubitus position, upper limbs along the body and cervical in neutral position during the time of interventions; and individuals will be free to discontinue the treatment at any time, and if they make the most recent data, they will be computed for analysis, as well as the reason for the interruption.

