#### Intervention description {11a}

The interventions will follow a standardized therapy protocol, and the assessments will be performed immediately before and after the single treatment session. Four acupuncture points (*Tianzhu*, *Fengchi*, *Jianjing*, and *Jianzhongshu*) will be stimulated bilaterally with needles, laser, or sham. The participant will be positioned in a ventral decubitus position, upper limbs along the body, and cervical in neutral position and asked to rest for 5 min, prior to the intervention. At the locations where the therapies will be applied, the skin will be hygienized with gauze and 70% alcohol solution. A dermatograph pencil (COLOURED®) will be used to draw circles with diameters of 2 cm around the application points. The same researcher, an acupuncturist with specialization in the field and 9 years of clinical experience, will perform all the interventions (R3). The individuals will be asked not to use any other treatment for neck pain during the study period. All the data collected about the participants will be confidential (Fig. 1).

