#### Criteria for discontinuing or modifying allocated interventions {11b}

There will be no changes in the allocations and no migration of individuals between the groups will be allowed. If individuals discontinue treatment, recent data will be computed for the analyses according to the intention-to-treat principle, and the motive for the desistence will be recorded.

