### Methods in analysis to handle protocol non-adherence and any statistical methods to handle missing data {20c}

In the case of discontinuity, missing data will be handled by adopting the intention-to-treat principle, in order to make statistical inferences.

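### The rule on recent data for participants who stop, offered as intention-to-treat, most naturally means carrying the last score forward, which can distort the 1-month pain comparison in either direction.

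*Protocol article*

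**What the plan says.** Three places in the protocol article deal with participants who stop:

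- Section 18b (retention and follow-up): "the most recent data will be computed, and analysis will be performed using the intention-to-treat principle".
- Section 11b (discontinuing interventions): "recent data will be computed for the analyses according to the intention-to-treat principle".
- The end of the exclusion criteria, in garbled form: "if they make the most recent data, they will be computed for analysis".

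Item 20c, the place reserved for missing data, says only that "missing data will be handled by adopting the intention-to-treat principle, in order to make statistical inferences". It does not mention recent data, and it names no model, no assumption about why data are missing and no sensitivity analysis.

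The schedule is short. Under the intervention description, "the assessments will be performed immediately before and after the single treatment session". The only later contact is described in section 11c: "as well as the follow-up 1 month after the end of the intervention, which will be performed by telephone". The primary objective covers NRS pain "immediately after the end of the therapies and with follow-up after 1 month". The sample size section plans for 20% loss and ties it to people who wish to break off the intervention.

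**The concern.** Intention-to-treat fixes the analysis set: everyone randomised, in the arm allocated. It supplies no value for a score that was never obtained. Item 20c therefore names a principle where a method is needed. The only operational instruction anywhere is the one about recent data, and its natural meaning is that the last available score stands in for the missing one.

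This design makes that awkward. A participant lost after the session has, as last score, a rating given just after treatment. A participant lost during or before the session has only the baseline. Either value would be entered as the 1-month NRS and treated as if it had been observed. Pain relief minutes after needling or laser need not resemble pain a month later, so the 1-month contrast would partly measure something else. Participants can tell needle from laser, as the limitations section accepts, so loss may also differ between arms. Unequal loss under carry-forward can produce a difference even when all arms follow the same course.

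**Working it through.** **Plan's own figure.** The inputs in the sample size section are a difference of 1.5 points, SD 1.6, power 80% and loss 20%. The significance level in the statistical methods is 0.05. A one-way ANOVA with three groups and a largest difference of 1.5 needs 23 per group (power 0.801). Then 23 × 1.2 = 27.6, rounded up to 28, and 3 × 28 = 84. The stated size reproduces and is not affected by this point.

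**Bias formula.** For each arm let *p* be the share lost and *c* the true 1-month mean minus the mean of the carried score. Replacing the lost scores shifts the arm's 1-month mean by −*p* × *c*. Lower NRS is better, so take benefit as sham minus active. Then

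bias in benefit = (*p* × *c*) in the active arm − (*p* × *c*) in the sham arm.

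**Assumptions not in the document.** Two-sided t-test of one active arm against sham, correlation 0.5 between scores, loss at random within each arm, and the fading pattern and timing of loss given in each case. From the document: 28 per arm and SD 1.6. Type I error is from simulation (20,000 to 40,000 trials per case).

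**A. Post-session score carried, 1.5-point immediate effect fully gone by 1 month, no change in sham.** Here *c* = 1.5 in the active arm and 0 in sham.

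| Loss, both arms | Bias | Type I error |
|---|---|---|
| 10% | 0.10 × 1.5 = 0.15 | 6.0% to 6.5% |
| 20% | 0.20 × 1.5 = 0.30 | about 10% |
| 30% | 0.30 × 1.5 = 0.45 | 16% to 17% |

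If sham also improves by 1 point and relapses, then *c* = 2.5 and 1.0. At 20% loss the bias is 0.50 − 0.20 = 0.30 again, with type I error 9.3%. Using only observed 1-month scores in that setting gives bias 0.00 and 4.9%.

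**B. Unequal loss, common course.** Both arms improve by 2 points and relapse fully, with loss of 30% in one arm and 10% in the other. Bias = 0.30 × 2 − 0.10 × 2 = 0.40 in favour of the arm with more loss, and type I error is about 13%.

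**C. Baseline carried, 20% loss in both arms.**
- No true 1-month effect: bias 0.00, type I error about 5%.
- A lasting 1.5-point effect: *c* = −1.5 in the active arm, so the estimate is 1.5 − 0.20 × 1.5 = 1.20. The effect is diluted.
- Half the losses carry baseline and half carry the post-session score, with the fading effect of case A: bias 0.15, type I error 6.3% to 6.5%.

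**D. Post-session score carried, effect persists at 1.5, equal loss.** Both arms have the same *c*, so the bias is 0. If the effect instead grows from 0.5 to 1.5, then at 20% loss the bias is 0.20 × (0.5 − 1.5) = −0.20, an understatement.

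**The case against.** Four points can be made for the plan.

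1. Carry-forward is never named. The sentences could mean only that data collected before withdrawal stay in the analysis. This stands as a possible reading. It is the weaker one, because keeping earlier data puts nothing in the place of a missing 1-month score, yet item 20c claims that missing data are dealt with. Under that reading the document has no working rule, and the wording still needs repair.
2. A reader might infer that the plan states a carry-forward rule that will manufacture a 1-month benefit. The document does not support that. The 20% loss is described as people breaking off the intervention, and with a single session many of them may have only a baseline score. Case C then applies: no false effect, and dilution of a real one. The direction of bias is not fixed by the text.
3. The larger figures need complete fading and all loss after the session. Neither is stated. Even the 0.30 at 20% loss is one fifth of the 1.5-point difference that the plan regards as relevant.
4. The immediate post-session NRS, the other primary time point, is taken at the treatment visit and is much less exposed. The 1-month assessment is a telephone call with message reminders, which should limit loss.

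It could also be said that missing-data detail belongs in an analysis plan that is not shown. That would answer a complaint about omitted detail. It does not answer this one, because the article does give a rule and does present intention-to-treat as a missing-data method, and an analysis plan that followed it would inherit both.

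**Conclusion.** The concern holds as a poorly fixed rule that should be corrected before analysis. Its natural reading puts a post-session or baseline score into a primary time point. If post-session scores are carried and an immediate 1.5-point effect fades completely, the false 1-month difference is 0.15 points at 10% loss and 0.30 at 20%, and at 20% the type I error roughly doubles from 5% to 10%. Unequal loss of 30% against 10% with a shared transient improvement gives 0.40 points and about 13%. Other equally permissible assumptions give no bias, or shrink a lasting 1.5-point effect to 1.2. All of these rest on the assumed correlation, fading pattern and timing of loss. They are a range of what could happen, not a prediction. The sample size and the design are not called into question.

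**What to change.** - In the exclusion criteria and in sections 11b and 18b, delete the wording on computing recent data. Keep the recording of reasons for stopping.
- In item 20c, keep intention-to-treat as the definition of the analysis set: all randomised participants in their allocated arm. As the missing-data method, replace it with a likelihood-based repeated-measures model (arm, time, arm by time, baseline NRS) on all observed NRS values, or with multiple imputation. State that no score is carried forward.
- Add one sensitivity analysis that lets missing 1-month scores differ systematically from observed ones, for example imputation shifted by a fixed amount.
- State that the 1-month call is still attempted for participants who stop early.

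The cost is rewording and a little more analysis work. The sample size and the set of planned assessments stay the same. The model assumes that data are missing at random given what was observed, which is why the sensitivity analysis is needed.
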